## Introduction

According to a recent estimate, about 425 million adults around the world and an estimated 158.8 million adults in the Western Pacific Region are living with diabetes mellitus (DM) [1]. Among the International Diabetes Federation regions, the Western Pacific Region has the highest number of adults living with DM [1, 2]. Moreover, the prevalence of both type 1 and type 2 DM (T2DM) has increased significantly during recent decades [3]. T2DM, being much more common, has been the main driver for the increase in global diabetes prevalence [3]. The results of the National Health and Nutrition Survey in Japan, released in September 2017, reported that there were an estimated 20 million patients with T2DM and prediabetes, of which 10 million patients had T2DM [4].

Hypertension is present in more than 50% of patients with T2DM and contributes significantly to microvascular and macrovascular diseases in T2DM [5]. Moreover, the incidence of cardiovascular disease markedly increases when the two diseases coexist [6]. Thus, intensive treatment of high blood pressure, in addition to hyperglycemia, is important for patients with T2DM.

Epidemiological studies have shown that excessive salt intake is directly related to cardiovascular mortality and to an increase in blood pressure [7]. Many hypertension guidelines recommend salt restriction, based on studies that have demonstrated a decrease in blood pressure with a reduction in salt intake [8, 9]. We have previously reported in a single-arm trial that nutritional instructions on dietary salt restriction by a national registered dietitian provided to patients with T2DM consuming excessive salt may be beneficial in reducing dietary salt intake and home blood pressure [10]. In that study, daily salt intake was significantly reduced by 0.8 g at 2 months and 0.7 g at 6 months after the instruction. Moreover, morning systolic blood pressure was significantly reduced by 2.7 mmHg at 2 months and 5.8 mmHg at 6 months after the instruction. However, dietitians are usually too busy to see patients during their regular clinic visits. Therefore, it would have great clinical significance if this study can demonstrate that shorter and more focused nutritional instructions given to patients by their regular physicians during regular outpatient visits are effective. It might contribute to reducing the financial burden on patients and also the need for patients to have separate consultations with a dietitian.

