## Methods

### Study design

The study will be an unblinded RCT aimed at testing whether instructions on dietary salt restriction provided by physicians during outpatient visits is effective in reducing salt intake in patients with type T2DM who have an excessive salt intake. A total of 200 patients with T2DM and excessive salt intake (150 from the Hospital of the Kyoto Prefectural University of Medicine, 50 from Kyoto First Red Cross Hospital according to the proportion of outpatients) will be randomly assigned to an intervention group or a control group, using permuted block randomization, with block sizes of ten. Spot morning urine tests will be performed, and the results will be used to estimate their salt intake. The primary outcome will be the change in daily salt intake between baseline and 24 weeks. Each participant will be enrolled for 24 weeks from randomization to the final follow-up assessment and will visit every 8 weeks (Fig. 1).

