#### Secondary outcomes

The secondary outcomes will include body weight, hemoglobin A1c, blood pressure, serum lipid profile (triglycerides and high-density lipoprotein cholesterol), estimated glomerular filtration rate, and urinary albumin excretion (UAE) [9]. Blood samples for biochemical measurements will be taken in the morning.

Hemoglobin A1c level, serum lipid profile, and other biochemical data will be determined using standard laboratory measurements. The UAE will be measured with an immunoturbidimetric assay. The hemoglobin A1c level will be expressed in National Glycohemoglobin Standardization Program units. Information on age, duration of diabetes, smoking status, alcohol consumption, and use of medication will be collected from each participant at baseline.

The presence of retinopathy will be assessed from chart reviews.

The presence of nephropathy will be assessed by dividing the UAE into three categories, as follows: normoalbuminuria, UAE < 30 mg/g Cr; microalbuminuria, 30–300 mg/g Cr; or macroalbuminuria, > 300 mg/g Cr.

Neuropathy will be defined based on the diagnostic criteria for diabetic polyneuropathy proposed by the Diabetic Neuropathy Study Group [16].

Macrovascular complications will be defined as the presence of previous cardiovascular disease, cerebrovascular disease, or arteriosclerosis obliterans, on the basis of clinical history or physical examination.

Changes in diabetic medication (number of drugs currently prescribed to the patient; dose of drugs; initiation of new medication during study period; initiation of injectable diabetic medication; initiation of insulin; number of medications stopped or changed during the study period) and changes in antihypertensive medication (number of drugs started and stopped during study period; dose of drugs; initiation of new medication during study period) will be recorded. We will exclude patients from the analysis who were newly prescribed or stopped thiazide diuretics and sodium glucose transporter 2 inhibitors during the study.

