### Statistical methods

A mixed model will be used to analyze the factors involved in sodium intake. Factors and changes in factors that may influence sodium intake will be adjusted in multivariate models. Subgroup analyses will be conducted stratified by age (< 65 years or ≥ 65 years), sex (male or female), body mass index (< 22%, or ≥ 22%), and hemoglobin A1c levels (< 7%, or ≥ 7%) to investigate the coherency of educational effect among subgroups. The secondary outcomes will be compared using separate regression models. The differences of values between the two groups with 95% confidence interval and a *p* value < 0.05 will also be presented. We will use an intention-to-treat analysis. JMP version 11.2.0 software (SAS Institute, Cary, NC, USA) will be used as the statistical software package for the analysis. All analyses will be two-sided, and *p* values < 0.05 will be considered statistically significant. Multiple imputations will be applied if there are missing values. In a previous study, it was shown that after patients with T2DM were given instructions on reducing salt intake, their salt intake declined from 10.3 ± 1.6 g to 9.3 ± 1.9 g per day [10]. Therefore, we have based our sample size calculation on the assumption that the intervention group will show a 1-g reduction in their daily salt intake, and that the salt intake in the control group will remain unchanged. With the two-sided significance level set at 5.0% and power set at 80%, the required sample size will be 90 participants in each group. Assuming a 10% dropout rate [17], a total of 200 participants will be required for both groups combined.

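### The salt-intake models adjust for changes measured after randomisation and are not marked as exploratory, so an arm effect taken from them can be biased and is not the intention-to-treat effect

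*Protocol article*

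**What the plan says.** All references are to the protocol article.

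- **Model (Statistical methods).** "A mixed model will be used to analyze the factors involved in sodium intake". The next sentence adds: "Factors and changes in factors that may influence sodium intake will be adjusted in multivariate models". The factors are not listed, and adjustment is not confined to baseline values.
- **Analysis principle (Statistical methods).** "We will use an intention-to-treat analysis".
- **Between-group result (Statistical methods).** "The differences of values between the two groups with 95% confidence interval and a *p* value < 0.05 will also be presented". This follows the sentence on secondary outcomes. It does not say whether the differences are adjusted, or whether they include the primary test.
- **Primary outcome (Study design).** "The primary outcome will be the change in daily salt intake between baseline and 24 weeks".
- **Changing factors that are recorded (Secondary outcomes).** "The secondary outcomes will include body weight, hemoglobin A1c, blood pressure, serum lipid profile", together with estimated glomerular filtration rate and urinary albumin excretion. Diabetic medication changes are recorded too. For blood-pressure drugs, the text is that "changes in antihypertensive medication (number of drugs started and stopped during study period; dose of drugs; initiation of new medication during study period) will be" documented.

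**The concern.** The trial asks whether physician instruction lowers salt intake. Randomisation answers that question for the total effect of allocation, and adjustment for baseline variables leaves that protection intact. Adjustment for variables measured after allocation does not, if allocation or the outcome affects them.

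Several recorded changes could be affected in this trial:

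- **Body weight.** One of the twelve tips in the Intervention section is against overeating, so weight change can be a result of the instruction. Weight is also a term in the equation that produces the outcome (Primary outcome section).
- **Blood pressure.** The Introduction cites studies in which pressure fell as salt intake fell, so a pressure change can be a consequence of the outcome.
- **Medication.** Physicians know the allocation (Allocation section), so prescribing during follow-up can differ by arm.

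Body weight and blood pressure are also secondary outcomes, so the trial itself treats them as possible effects of the intervention. If a change-adjusted model supplied the reported arm effect, the estimate would depend on which changes were entered and would not be the effect of the instruction.

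**Working it through.** **Plan's own figures.** The planned effect is 1 g/day, with two-sided 5% significance, 80% power and 90 per group. Using n = 2(1.96 + 0.84)² SD²/1², the printed SDs give 41 (SD 1.6) and 57 (SD 1.9). The SD of a change at zero correlation, √(1.6² + 1.9²) = 2.48, gives 97. The stated 90 implies an SD of about 2.39, which is not printed. The dropout step reproduces: 90/0.9 = 100 per group, 200 in total. The sample size does not decide this point; it supplies only the 1 g reference and a range of SDs.

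**General rule.** In a linear model, adding a post-randomisation covariate C shifts the arm coefficient by (within-arm slope of salt change on C) × (arm difference in C).

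**Case A: C is purely a consequence of salt change.** Let r be the within-arm correlation (assumed).

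- Slope of salt on C = r × SD(salt)/SD(C).
- Arm difference in C = r × SD(C)/SD(salt) × 1 g.
- Product = r² × 1 g. The SDs cancel.

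| r | Removed from 1 g | Remaining |
|---|---|---|
| 0.2 | 0.04 g | 0.96 g |
| 0.3 | 0.09 g | 0.91 g |
| 0.5 | 0.25 g | 0.75 g |

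A simulation with 200,000 subjects and a true effect of −1 g gave adjusted coefficients of −0.92 (r = 0.3) and −0.75 (r = 0.5), in agreement.

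**Case B: C is a mediator carrying a share m of the effect (assumed).** The adjusted coefficient estimates (1 − m) × 1 g. The power columns take 90 per group and hold the SD fixed, using power = Φ{(1 − m)/(SD√(2/90)) − 1.96}.

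| m | Expected | Simulated | Power, SD 2.48 | Power, SD 1.9 |
|---|---|---|---|---|
| 0 | 1.0 g | −0.99 | 77% | 94% |
| 0.1 | 0.9 g | −0.90 | 68% | 89% |
| 0.3 | 0.7 g | −0.70 | 47% | 70% |
| 0.5 | 0.5 g | −0.49 | 27% | 42% |

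The power figures are approximate. Adjustment also lowers the residual SD, while correlation between arm and covariate raises the standard error.

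**Body weight in the equation.** Estimated intake is proportional to the bracketed body-size term raised to 0.392. For an assumed person of 68 kg, 165 cm and 65 years, that term is 14.89×68 + 16.14×165 − 2.04×65 − 2244.45 = 1298.6. Losing 1 kg lowers it by 14.89/1298.6 = 1.15%, and so lowers intake by about 0.45%. On an intake of 9.3 g that is about 0.04 g per kg. The mechanical link is real but small.

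**When nothing is lost.** If allocation does not affect a change, and the change is not a consequence of salt intake, the shift is zero.

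**The case against.** The strongest reply is that the change-adjusted models may never have been meant as the treatment-effect estimate. The mixed model is introduced as an analysis of factors involved in intake, the adjusted models are plural, and between-group differences are also to be presented under intention to treat. On that reading these are association analyses and legitimate as such. This stands in part: a reader might infer that the adjusted model is the headline estimate, and the article does not say so. It does not rule it out either. This is the only model named for the primary outcome, nothing labels its adjusted form exploratory, and the sentence on group differences does not say that they are unadjusted.

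A second reply is that the sentence covers factors that may influence intake, so blood pressure, a likely consequence of intake, may not be meant. That is fair. Since no list is given, blood pressure can be used only as an example. Weight and medication remain candidates.

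A third concerns size. The Introduction reports that "morning systolic blood pressure was significantly reduced by 2.7 mmHg at 2 months and 5.8 mmHg at 6 months after the instruction", and a reader might take 2.7 to 5.8 mmHg as an arm difference. With an assumed SD of pressure change of 12 mmHg, a salt-change SD of 2.38 g and r of 0.2 to 0.5, that would give 0.2 × 2.38/12 × 2.7 = 0.11 g up to 0.5 × 2.38/12 × 5.8 = 0.58 g. The document does not support this. Those falls are before-and-after changes in a single-arm study of dietitian instruction, with no comparator. They also do not fit a pathway through salt alone: at r = 0.3 the slope is 0.3 × 12/2.38 = 1.5 mmHg per g, so a 1 g effect gives about 1.5 mmHg and not 5.8. Larger losses would need an effect on pressure that bypasses salt.

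**Conclusion.** The point holds in a limited form. The plan commits to adjusting the sodium-intake models for changes that arise after randomisation, and it does not keep those models apart from the treatment-effect estimate. Followed as written, it can yield an arm coefficient that is not the intention-to-treat effect.

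The documents give no figure for the bias. The losses of 0.04 to 0.25 g (consequence of salt change) and 0.1 to 0.5 g (mediator), out of 1 g, rest on assumed correlations and mediated shares.

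A reader might infer that the adjustment necessarily shrinks the effect. That goes too far. The bias is nil for changes unaffected by allocation or outcome. It can also run in other directions if a change shares unmeasured causes with salt intake, or if the instruction moves a covariate in a way that offsets its benefit. The statement supported here is that the effect can be attenuated or otherwise biased.

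**What to change.** In Statistical methods:

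1. State that the primary between-arm estimate at 24 weeks comes from a mixed model with arm, visit and arm-by-visit terms, adjusted only for baseline covariates: baseline salt intake, site and any other baseline factors named in advance.
2. Delete the reference to changes in factors from that model, and apply the same limit to any other model reported as a treatment effect.
3. If models containing changes in weight, medication, blood pressure or similar are wanted, keep them under a separate label as exploratory association or mediation analyses. Do not report their arm coefficient as the treatment effect.

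The cost is wording only. No new data, visits or change in sample size are needed. The change should be made, and dated, before outcome data are compared by arm.

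### Consistency of effect across subgroups is to be judged from stratified analyses under a general p < 0.05 rule, with no between-subgroup comparison named

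*Protocol article*

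**What the plan says.** All of this stands in the Statistical methods section of the protocol article.

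- **Method:** "Subgroup analyses will be conducted stratified by age (< 65 years or ≥ 65 years), sex (male or female), body mass index" and HbA1c. That is four binary factors, or eight strata.
- **Purpose:** "to investigate the coherency of educational effect among subgroups".
- **Significance rule:** "All analyses will be two-sided, and *p* values < 0.05 will be considered statistically significant". The subgroup analyses are neither exempted from this rule nor labelled exploratory.
- **Between-subgroup comparison:** none is named, and there is no rule for deciding whether the effect counts as consistent.

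The same section plans a mixed model for salt intake, and promises between-group differences with 95% confidence intervals.

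**The concern.** The question is whether the effect of the advice is the same in different kinds of patient. That is a question about the difference between two stratum effects. The method named gives an effect and a p value within each stratum, and these do not answer it. One stratum can be significant and the other not when the two effects are identical, simply because each holds only part of the sample.

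At stake is a report that brief advice from a physician works in, say, women or older patients only, when the data show no such thing. The primary comparison is not affected.

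**Working it through.** **Inputs from the protocol (Statistical methods)**

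- Effect: "the intervention group will show a 1-g reduction in their daily salt intake", with no change in the control group, so a difference of 1 g.
- Error rates: "With the two-sided significance level set at 5.0% and power set at 80"%.
- Size: "the required sample size will be 90 participants in each group", and 200 in total after 10% dropout.
- Spread: "their salt intake declined from 10.3 ± 1.6 g to 9.3 ± 1.9 g per day". The SD used in the sample-size calculation is not stated.

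**Assumptions**

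Subgroup sizes are not given, so 50:50 splits are assumed, with other splits shown below. The true effect is taken to be the same in every subgroup. Consistency is taken to be read from within-stratum p values.

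**Step 1: the plan's own figure**

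Use n per group = 2 × SD² × (1.96 + 0.84)² / 1², with a small-sample correction.

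| SD (g) | Source | n per group |
|---|---|---|
| 1.6 | quoted, before | 41 |
| 1.9 | quoted, after | 57 |
| 1.76 | pooled, √((1.6² + 1.9²)/2) | 49 |
| 1.77 | change, correlation 0.5 | 50 |
| 2.48 | change, correlation 0 | 97 |

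None gives 90. The dropout step does reproduce: 180 / 0.90 = 200. Working backwards, 90 per group at 80% power implies an SD of about 2.38 g (t test) or 2.39 g (normal approximation). Because the SD is unstated, the results below are given for 2.38 and also for the pooled 1.76.

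**Step 2: power in one stratum**

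With 45 per arm, the standard error is 2.38 × √(2/45) = 0.50 g, so the expected z is 1/0.50 = 2.0 against a critical value of 1.96. Power is about 50%. With SD 1.76 it is about 76%.

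**Step 3: disagreement within one factor**

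The strata of one factor contain different patients, so P(exactly one significant) = p₁(1 − p₂) + p₂(1 − p₁).

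- SD 2.38, 50:50: 2 × 0.50 × 0.50 = 0.50.
- SD 1.76, 50:50: 2 × 0.76 × 0.24 = 0.36.
- Other splits at the implied SD: 0.51 at 40:60, 0.55 at 30:70 and 0.61 at 20:80.

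**Step 4: at least one of four factors**

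The four factors divide the same patients, so the four disagreements are correlated and cannot be multiplied together. Trials were simulated with 90 per arm, a uniform effect and four independent 50:50 factors.

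| Uniform true effect | SD (g) | At least one factor disagrees |
|---|---|---|
| 1.0 g | about 2.38 | about 80% |
| 1.0 g | 1.76 | about 63% |
| 0.7 g | about 2.39 | about 70% |
| 0.5 g | about 2.39 | about 53% |
| 0 | about 2.39 | about 26% |

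**Step 5: the interaction test on the same data**

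Its false-positive rate is 5% per factor and 1 − 0.95⁴ = 0.185 for any of four; simulation gives about 19%.

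For its power against a true 1 g difference between strata, the standard error at 50:50 is 2.39 × √(2/45 + 2/45) = 0.71 g, so z = 1/0.71 = 1.40 and power is about 29%. At 20:80 (18 and 72 per arm) the standard error is 2.39 × √(2/18 + 2/72) = 0.89 g, and power is about 20%.

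**The case against.** The strongest reply is that the text contains no faulty decision rule. Stratifying by a factor is compatible with also fitting an interaction term, and the mixed model has room for one. The p < 0.05 sentence is a general statement of alpha and does not say how consistency will be judged. Stratum estimates with confidence intervals are a legitimate description. The article is condensed, and heterogeneity testing is often left to a statistical analysis plan. The subgroups are few and prespecified with cut-points, and the remedy has low power.

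Much of this stands, and it rules out three stronger readings that a reader might infer:

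- **That interaction tests have been replaced or ruled out.** The protocol is silent on them, and silence does not exclude them.
- **That any differences seen will mostly be chance.** This needs a truly homogeneous effect, which the documents cannot settle, and strata read by their p values, which the text does not state.
- **That at least one factor will disagree in 94% of trials.** This comes from 1 − 0.5⁴ = 0.94, which treats the four disagreements as independent. Even when the factors are independent, the disagreements are not, because they share the same patients and the same overall estimate. The figure is about 80%.

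What the reply does not remove is that the section itself links a purpose to a method. It asks about consistency, names stratified analyses as the way to examine it, and sets one significance rule for everything. That is a choice fixed in the text, and without a between-subgroup comparison it does not answer its own question.

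**Conclusion.** The point holds as a cheap improvement to a secondary analysis. As written, the protocol ties a question about consistency to a method that does not test it, and the general significance rule invites stratum-by-stratum reading.

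If the strata are read that way, a uniform 1 g effect would look inconsistent for about half of the factors, and for at least one of the four in about 80% of trials. Interaction tests would do so for 5% of factors and in about 19% of trials. These figures rest on 50:50 splits, a homogeneous effect, and the implied SD of about 2.38 g, which the protocol does not state. With SD 1.76 g they fall to 36% of factors and about 63% of trials, so the conclusion does not depend on that SD.

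**What to change.** Add to the Statistical methods section:

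- Consistency will be examined by arm-by-subgroup interaction terms in the planned mixed model, fitted to all patients, one factor at a time, for the week 24 effect.
- The interaction estimate will be reported with its 95% confidence interval (and p value), next to the stratum estimates with their intervals.
- No claim of significance will be made for a single stratum, and the subgroup results are exploratory.

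In the same edit, correct the unit of the body mass index cut, which is printed as a percentage. This is a clerical slip and has no bearing on the argument.

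The cost is a few lines of text and of analysis, with no new data or patients. The downside is low power: about 20% to 29% for a true 1 g difference between strata at the implied SD. Most interaction results will be inconclusive, and the report should say that a non-significant interaction does not show that the effect is consistent.

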#### Control group

During their baseline visit, participants allocated to the control group will be informed of their current salt intake but will not be given instructions by their physician on how to reduce their salt intake. Their physician will give them the same dietary guidance that is routinely given to patients during outpatient visits.

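### The 1 g planning effect disagrees with the 0.7 g that the protocol itself reports from the same study at 6 months, so the 80% power applies to an effect about 43% larger than the one cited for the primary time point

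*Protocol article*

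**What the plan says.** Two sections of the protocol describe the result of one earlier study, reference [10], and they differ.

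- **Statistical methods.** Intake in that study is given as 10.3 (1.6) g per day before instruction and 9.3 (1.9) g after it, a fall of 1.0 g with no time point given. From this the protocol concludes: "we have based our sample size calculation on the assumption that the intervention group will show a 1-g reduction in their daily salt intake". It further assumes no change among controls. The result is: "power set at 80%, the required sample size will be 90 participants in each group". A 10% dropout allowance brings the total to 200.
- **Introduction.** In the same study, described as a single-arm trial with a dietitian, "daily salt intake was significantly reduced by 0.8 g at 2 months and 0.7 g at 6 months after the instruction".

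On timing, the Study design section says: "The primary outcome will be the change in daily salt intake between baseline and 24 weeks". Measurements and outcomes calls the last visit the 6-month visit. The Abstract and the Primary outcome section list 8, 16 and 24 weeks without choosing among them, so 24 weeks as the primary time point rests on the Study design section.

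On the comparator, control participants "will be informed of their current salt intake but will not be given instructions".

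**The concern.** The planning effect is presented as what reference [10] found, not as a smallest difference worth detecting. Yet neither time point in the Introduction shows 1 g, and the one that matches the primary outcome shows 0.7 g. Since 1.0 / 0.7 = 1.43, the planning effect is about 43% larger than the protocol's own 6-month figure.

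The control arm raises a related difficulty. The earlier study had no control group and enrolled patients with excessive intake, so its before-after change includes any regression to the mean. Here both arms are selected for high intake on a spot-urine estimate, and controls are told their result. Some fall among controls is plausible, and it would be subtracted from the between-group difference.

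At stake is how the trial is read. Anyone relying on the 80% would take a non-significant result as stronger evidence against physician guidance than the sample may justify.

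**Working it through.** **Inputs.** From Statistical methods: two-sided 5%, 80% power, 90 per group, difference 1 g (1 g in the intervention arm, 0 in controls), and printed values 1.6 and 1.9, read as standard deviations (SDs). From the Introduction: 0.8 g and 0.7 g. The SD used in the calculation is not stated.

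**1. The plan's own figure.** With the normal approximation, n per group = 2 × SD² × (1.960 + 0.8416)² / d². At d = 1 g:

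| SD | Source | n per group |
|---|---|---|
| 1.6 | printed, before | 41 |
| 1.76 | pooled, √((1.6² + 1.9²)/2) | 49 |
| 1.9 | printed, after | 57 |
| 2.48 | change score, zero correlation, √(1.6² + 1.9²) | 97 |

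None of these gives 90. Solving for the SD that does: √(90/2) / 2.8016 = 2.39. That equals a change-score SD with a before-after correlation of about 0.07. The dropout step reproduces: 90 / 0.90 = 100 per group, 200 in total.

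**2. Power at the Introduction's figures, taking 90 per group and 80% at 1 g as stated.** The expected test statistic at 1 g is then 2.80, and it scales with the effect.

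- At 0.8 g: 0.8 × 2.80 = 2.24; power = Φ(2.24 − 1.96) = 61%.
- At 0.7 g: 0.7 × 2.80 = 1.96; power = Φ(1.96 − 1.96) = 50%.

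This step needs no separate SD, only that the plan's own statement is true. At the implied SD, 80% power at 0.7 g would take 184 per group.

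**3. Power at 0.7 g with the printed SDs applied directly.** Standard error = SD × √(2/90) = SD × 0.149.

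| SD | Standard error | 0.7 / standard error | Power at 0.7 g |
|---|---|---|---|
| 1.9 | 0.283 | 2.47 | 69.5% |
| 1.76 | 0.262 | 2.67 | 76% |
| 1.6 | 0.239 | 2.93 | 83.5% |

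A non-central t calculation agrees within about 0.5 percentage points.

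**4. Where the shortfall ends.** 90 per group reaches 80% at 0.7 g only if the SD is at most 0.7 × 2.394 = 1.68. For a change score built from the printed SDs, that needs a before-after correlation of about 0.55 or more.

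**5. Control arm.** If the intervention arm falls by 0.7 g and controls fall by c, the difference is 0.7 − c. Every c above zero lowers all the powers above. The documents give no basis for a value of c, so none is computed.

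**The case against.** The strongest reply is that the 50% is conditional. It depends on an SD of about 2.39 that is printed nowhere and is recovered from a sample size that the printed SDs do not reproduce. With those SDs, 90 per group has 94% to 99% power at 1 g and 69.5% to 83.5% at 0.7 g. The protocol also plans a mixed model with adjustment. If that includes baseline intake (an assumption), SD 1.9 with a correlation of 0.3 or 0.5 gives 74% or 81% at 0.7 g. This stands: the size of the shortfall is a range, and one end of it shows none.

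A reader might therefore go too far in three ways.

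- *The design delivers only 50% power.* The documents do not fix the SD, so no single figure can be asserted.
- *0.7 g is the correct planning value.* The 10.3 and 9.3 g may come from another time point or subset of reference [10]. The intervention arm here also hears its intake again at 8 and 16 weeks, and the Introduction does not say whether the earlier study did this. The documents support reconciling the figures, not replacing one with the other.
- *The protocol claims evidence for an unchanged control arm.* It states this as an assumption. The fair criticism is that the cited single-arm study cannot support it.

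It is also fair that the planned 95% confidence intervals would show whether 0.7 g is excluded, so a null result need not be misread. None of this explains why one reference yields both 1.0 g and 0.7 g.

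**Conclusion.** The point holds as an internal contradiction in a figure on which the sample size rests. The protocol derives 1 g from a study that it elsewhere reports as showing 0.7 g at the time of its primary outcome, and it does not explain the difference. The 80% power is therefore not established for the effect previously seen at 6 months.

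Power at 0.7 g runs from 50%, if the statement of 90 per group for 80% at 1 g is taken at face value, to about 84% at the smallest printed SD. The range rests on three assumptions: 24 weeks is the primary time point, 90 per group are analysed, and controls do not change. If controls fall at all, the whole range moves down.

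**What to change.** In Statistical methods:

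- Reconcile the 1.0 g with the 0.8 g and 0.7 g from reference [10], giving the time point and patient set behind each.
- State the SD used, whether it is for a single value, a change or a baseline-adjusted value, and its source.
- Restate the power of 90 per group at 0.7 g for that SD. Until the SD is given, quote the range of about 50% to 84%, not one figure. Alternatively, declare 1 g a target difference, justify it as such, and state the power at the previously observed 6-month effect.
- Say that an unchanged control arm is an assumption without support from the single-arm study, and that a fall among controls would lower power.

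The cost is a few sentences and a less favourable stated power. No extra patients are needed, and the analysis and conduct of the trial do not change.
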